### Psychometric evaluation and measurements

All patients complete the Hospital Anxiety and Depression Scale (HADS [32]) and the Pain Sensitivity Questionnaire (PSQ [33]) preoperatively, since higher grades of anxiety, depression or pain sensitivity are known to impair the patient’s satisfaction with medical treatments [34, 35]. Postoperatively, all patients answer the Anaesthesiologic Questionnaire for Patients (ANP [30]) and the German version of the patients’ satisfaction with anaesthesia questionnaire of [name] [36].

The ANP consists of several symptom and three different satisfaction scores — satisfaction with recovery, with general perioperative care and with anaesthesia — of which the latter represents our primary endpoint.

After the operation, the surgeon and the anaesthetist each rate their satisfaction with the patient’s coughing and pressing, the collapse of the lung and the general feasibility of the procedure on numeric rating scales (NRSs) from 0 to 10.

Postoperatively, a screening for delirium is performed daily by the ward nurses, using the Nursing Delirium Screening Scale (Nu-DESC [37]) and the Confusion Assessment Method (CAM [38]) which together can detect delirium with a sensitivity of 83−100*%* and a specificity of 81−89*%* [39]. Pain is recorded daily using an NRS from 0 to 10. All complications will be recorded. Standard measurements such as operation time, hospital length of stay, drainage treatment time, serum C-reactive protein and analgesic consumption will be documented as part of the clinical routine (Fig. 2).

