### Randomisation and preference arms

Eligible patients are randomised with variable block size without stratification to the control (GA) or test group (LA) as shown in Fig. 1. Patients are allocated using the built-in randomisation module of the electronic data capture (EDC) software (see the following section on “Data management and confidentiality”).

Patients who refuse to be randomised are asked to attend the preference arm. They may choose their form of anaesthesia. The preference arm is not limited to a certain sample size. Recruitment ends when the randomised arms achieve the calculated sample size.

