### Hypothesis and sample size calculation

The null hypothesis is that patients with LA are as satisfied with anaesthesia according to the “satisfaction with anaesthesia” score of the ANP as those with GA. The alternative hypothesis is that satisfaction in both groups is not equal. The score is noted on an ordinal scale from 0 to 3. The mean satisfaction in the evaluation study was *μ*=2.58 with a standard deviation of *σ*=0.54 [30]. A difference of satisfaction of *ε*=0.32 point is defined as clinically relevant, resulting in a mid-scale effect size *ε*/*σ*=0.59. With a significance level of *α*=5*%*, a power of (1−*β*)=80*%* and an allocation rate of 1:1, we need 
$$ n=\left(1+\frac{1}{1} \right) * \left(\sigma * \frac{Z_{(1-{\alpha}/{2})} + Z_{(1-\beta)} }{\epsilon}\right)^{2}=45 $$ patients in each randomised group [40]. Since the ANP satisfaction scale is ordinal, we correct the sample size by +10%. Furthermore, we expect a dropout rate of 10%. In summary, 2∗45∗1.1∗1.1=108 patients will be included in the randomisation group of the study.

Statistical analyses will be performed using the statistical language R. Data will be presented using descriptive statistics such as frequency or mean and standard deviation. Individual changes from baseline to the end of treatment will be analysed if appropriate. After checking for normal distribution, the primary endpoint will be tested with Student’s *t* test or the Mann-Whitney *U* test, respectively. There will not be an interim analysis for the primary endpoint. Multivariate analysis will be performed to identify independent variables which then can be the focus of further investigations.

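### The primary test ignores baseline anxiety, depression and pain sensitivity scores that the protocol collects as prognostic; it is valid but probably less precise than the data allow

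*Protocol article*

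**What the plan says.** Under Psychometric evaluation and measurements, the protocol article has all patients fill in the HADS and the PSQ preoperatively. Its reason is prognostic: "since higher grades of anxiety, depression or pain sensitivity are known to impair" satisfaction with medical treatments.

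Under Hypothesis and sample size calculation, the primary endpoint (the ANP satisfaction-with-anaesthesia score, range 0 to 3) is compared by Student's t test or the Mann-Whitney U test, depending on a check for normality. Neither test takes a covariate. The hypothesis is two-sided: "The alternative hypothesis is that satisfaction in both groups is not equal". The sample size rests on a mean of 2.58 "with a standard deviation of *σ*=0.54", and "A difference of satisfaction of *ε*=0.32 point is defined as clinically relevant". The only multivariable step has another purpose: "Multivariate analysis will be performed to identify independent variables which then can be the focus of further investigations". It names no covariates.

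The design does not balance the scores either. Under Randomisation and preference arms: "Eligible patients are randomised with variable block size without stratification".

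**The concern.** The protocol gives a prognostic reason for collecting these scores but uses them neither in the randomisation nor in the primary comparison. If they predict the outcome, a pre-specified adjusted analysis of the same patients would give a narrower interval and more power. The sample size was set for only 80% power, so a few points matter.

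This is not a detail left to an analysis plan. The article names the primary test, and the test it names is unadjusted.

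**Working it through.** **1. The plan's own figure.** Inputs, all from Hypothesis and sample size calculation: two-sided α = 5%, power 80%, σ = 0.54, ε = 0.32, allocation 1:1.

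n = 2 × (0.54 × (1.960 + 0.842) / 0.32)² = 44.7, so 45 per group, as stated. The total is 2 × 45 × 1.1 × 1.1 = 108.9, against the stated 108. The calculation reproduces and matches the unadjusted test.

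**2. Evaluable patients.** 54 per arm less 10% dropout is 54 × 0.9 = 48.6, taken as 48.

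**3. Effect of adjustment.** If the three scores (HADS anxiety, HADS depression, PSQ) jointly explain a share R² of the outcome variance, the residual SD is 0.54 × √(1 − R²). The noncentrality is 0.32 / (residual SD × √(2/48)). Power comes from the noncentral t with 94 degrees of freedom unadjusted, or 91 with three covariates. The document gives no R², so the values below are assumptions.

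| Assumed R² | Residual SD | Noncentrality | Power at 48 per arm | Equivalent extra patients, 1/(1 − R²) − 1 |
|---|---|---|---|---|
| unadjusted | 0.540 | 2.90 | 81.9% | – |
| 0 (adjusted) | 0.540 | 2.90 | 81.9% | 0% |
| 0.05 | 0.526 | 2.98 | 83.8% | 5% |
| 0.10 | 0.512 | 3.06 | 85.7% | 11% |
| 0.20 | 0.483 | 3.25 | 89.5% | 25% |

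**4. With the plan's own 10% ordinal correction.** The effective number is 48 / 1.1 = 43.6 per arm. Unadjusted power is 78.1%; adjusted power is 80.1%, 82.2% and 86.4% at R² of 0.05, 0.10 and 0.20. Undoing both inflation factors from 108 instead gives 108 / (2 × 1.1 × 1.1) = 44.6 per arm and 79.1% unadjusted. The gain is of the same order on either basis.

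**5. What missing baseline scores could cost.** If patients without HADS or PSQ were dropped, 10% missing with R² = 0.10 would give 81.8%, and 5% missing with R² = 0.05 would give 81.9%. Either would cancel the gain. The missing shares are illustrative.

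**6. Ceiling.** The mean lies (3 − 2.58) / 0.54 = 0.78 SD below the maximum score. This may limit how much variance any baseline score can explain.

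**The case against.** The strongest reply is that nothing here is an error. An unadjusted two-group test in a randomised trial keeps its type I error, and the sample size was computed for that test with the matching SD. Measuring a prognostic score does not oblige a trial to put it in the primary test; it can also describe the sample or help compare the randomised and preference arms. This stands, and it limits the point to precision.

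Four stronger readings are tempting and should be set aside.

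- **That chance imbalance biases the result.** At 48 per arm, a covariate difference of up to 1.96 × √(2/48) = 0.40 SD is within ordinary chance. With an assumed correlation of 0.3, it would move the estimate by 0.3 × 0.40 × 0.54 = 0.065 points. The unadjusted standard error already allows for such shifts, so this is the precision argument again. Unstratified randomisation is not a fault.
- **That the power loss is established.** The protocol ties these traits to satisfaction with medical treatments in general and gives no figure for the ANP anaesthesia score. A gain to 86–90% needs an R² of 10–20%, which nothing in the document supports or excludes.
- **That the protocol confines HADS and PSQ to the exploratory analysis.** No covariates are named for it, so this would be inference.
- **That the change is wording only.** Anaesthetic and surgical procedures has the patient randomised and then informed about the planned anaesthesia; the questionnaires are only described as preoperative. The timeline figure, not shown here, may settle the order. A patient who knew the arm when completing the HADS could have an anxiety score affected by it, and adjusting for that score could bias the comparison. By December 2018, 27% of the sample was enrolled (0.27 × 108, about 29 patients), and timing for them can only be verified.

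The timing and missing-data objections are sound, but both can be met.

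**Conclusion.** The point holds as a matter of efficiency. The primary analysis leaves out baseline scores that the protocol itself regards as prognostic, and it is probably less precise than the data allow. At 48 evaluable per arm, power would rise from about 82% to 84%, 86% or 90% for an R² of 5%, 10% or 20%. At 0% there is essentially no loss, so the case for adjusting does not depend on the assumed value. The size of the gain does, and the ceiling may keep it at the low end.

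The conclusion rests on three conditions: the plan's SD and difference, baseline scores that allocation could not have affected, and no patients lost for missing covariates. The unadjusted test remains valid and the sample size stands on its own terms. This is a change worth making, not a flaw that undermines the trial.

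**What to change.** 1. Pre-specify one primary analysis: a linear model of the ANP anaesthesia satisfaction score on arm, HADS anxiety, HADS depression and PSQ (continuous), with robust standard errors. The arm coefficient is a difference in means, the scale on which 0.32 was defined. A single named model also removes the choice of test after a normality check.
2. Impute missing baseline scores simply, for example by the overall mean, blind to arm, so that no patient is dropped for a missing covariate.
3. Report the unadjusted comparison beside it, and keep the multivariate search exploratory.
4. Adjust only for scores completed before the patient learned the allocation. Confirm this for patients already enrolled and require it from now on. If it cannot be confirmed, keep the unadjusted comparison as primary and the adjusted one as a sensitivity analysis.

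The cost is slightly more analysis work and a check on questionnaire timing. No new measurements or patients are needed.

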**Fig. 2 Fig2:**
[figure not shown]
SPIRIT-conforming timeline of study procedures and outcome assessment

### Hypothesis and sample size calculation

The null hypothesis is that patients with LA are as satisfied with anaesthesia according to the “satisfaction with anaesthesia” score of the ANP as those with GA. The alternative hypothesis is that satisfaction in both groups is not equal. The score is noted on an ordinal scale from 0 to 3. The mean satisfaction in the evaluation study was *μ*=2.58 with a standard deviation of *σ*=0.54 [30]. A difference of satisfaction of *ε*=0.32 point is defined as clinically relevant, resulting in a mid-scale effect size *ε*/*σ*=0.59. With a significance level of *α*=5*%*, a power of (1−*β*)=80*%* and an allocation rate of 1:1, we need 
$$ n=\left(1+\frac{1}{1} \right) * \left(\sigma * \frac{Z_{(1-{\alpha}/{2})} + Z_{(1-\beta)} }{\epsilon}\right)^{2}=45 $$ patients in each randomised group [40]. Since the ANP satisfaction scale is ordinal, we correct the sample size by +10%. Furthermore, we expect a dropout rate of 10%. In summary, 2∗45∗1.1∗1.1=108 patients will be included in the randomisation group of the study.

Statistical analyses will be performed using the statistical language R. Data will be presented using descriptive statistics such as frequency or mean and standard deviation. Individual changes from baseline to the end of treatment will be analysed if appropriate. After checking for normal distribution, the primary endpoint will be tested with Student’s *t* test or the Mann-Whitney *U* test, respectively. There will not be an interim analysis for the primary endpoint. Multivariate analysis will be performed to identify independent variables which then can be the focus of further investigations.

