**Methods:**

Patients presenting for minor thoracoscopic surgery and physical eligibility for GA and LA are randomised to surgery under GA (control group) or LA (intervention group). Those who refuse to be randomised are asked to attend the study on the basis of their own choice of anaesthesia (preference arm) and will be analysed separately. The primary endpoint is patient satisfaction according to a psychometrically validated questionnaire; secondary endpoints are complication rates, capnometry, actual costs and cost effectiveness. The study ends after inclusion of 54 patients in each of the two randomised study groups.

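### The printed sample-size equation is wrong (108.9, not 108) and multiplying by 1.1 does not offset a 10% dropout; the effect on power is small and depends on what the ordinal scale costs

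*Protocol article*

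**What the plan says.** In the protocol article, section Hypothesis and sample size calculation, the target is built in three steps.

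- A two-sided comparison of two means ("The alternative hypothesis is that satisfaction in both groups is not equal") at 5% significance and 80% power, using a 0.32-point difference "with a standard deviation of *σ*=0.54", gives 45 patients per group.
- 10% is added because the satisfaction scale is ordinal.
- An allowance for loss follows: "Furthermore, we expect a dropout rate of 10" per cent.

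The steps are combined as "In summary, 2∗45∗1.1∗1.1=108 patients will be included". The Methods part of the abstract carries the result forward as a stopping rule for recruitment: "The study ends after inclusion of 54 patients in each of the two randomised study groups". The sections Randomisation and preference arms and Approval, end of study, registration also tie the end of recruitment and of the study to the calculated size.

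**The concern.** Two things in the last line do not hold.

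First, the equation as printed is false. The factors multiply to more than 108, and a required sample size is rounded up, not down.

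Second, adding 10% to a target and then losing 10% of the enlarged number does not return the target, because 1.1 × 0.9 = 0.99. The dropout step therefore falls short of its purpose even before rounding.

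Both slips run in the same direction. What is at stake is whether the number that ends recruitment supports the power stated for the primary endpoint, and whether a reader can reproduce that number from the printed inputs.

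**Working it through.** **Inputs**, all from Hypothesis and sample size calculation: two-sided α = 0.05; power 0.80; difference ε = 0.32; σ = 0.54, so ε/σ = 0.593; allocation 1:1; ordinal correction +10%; dropout 10%. The 54 per arm is in the abstract.

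**1. Base size (plan's figure reproduced).** n = 2 × [0.54 × (1.960 + 0.8416) / 0.32]² = 44.70, rounded up to 45 per arm. This step is correct.

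**2. The printed product.** 2 × 45 × 1.1 × 1.1 = 108.9, or 54.45 per arm. Rounding up gives 109, or 110 for equal arms. Carrying the unrounded base gives 2 × 44.70 × 1.21 = 108.18, which also rounds up to 109.

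**3. The dropout step.**
- Evaluable patients required after the ordinal correction: 45 × 1.1 = 49.5 per arm.
- Evaluable patients left from 54 per arm: 54 × 0.9 = 48.6, short by 0.9 per arm.
- Without rounding down: 54.45 × 0.9 = 49.0, still below 49.5.
- Dropout divided out: 49.5 / 0.9 = 55 per arm, 110 in total.

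Of the two-patient gap between 108 and 110, 0.9 comes from rounding down (108.9 − 108) and 1.1 from the dropout step (110 − 108.9).

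**4. Power.** The normal approximation is Φ(0.593 × √(n/2) − 1.960). The t figure uses the noncentral t distribution with 2n − 2 degrees of freedom and noncentrality 0.593 × √(n/2). The ordinal scale is treated in two ways: it costs nothing (n is the evaluable number), or it costs the plan's full allowance (n is the evaluable number divided by 1.1).

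| Randomised per arm | Evaluable per arm | Ordinal cost | Effective n per arm | Power, normal | Power, t |
|---|---|---|---|---|---|
| 54 | 48.6 | none | 48.6 | 83.2% | 82.4% |
| 54 | 48.6 | full 10% | 44.2 | 79.5% | 78.6% |
| 55 | 49.5 | none | 49.5 | 83.8% | 83.1% |
| 55 | 49.5 | full 10% | 45.0 | 80.3% | 79.4% |

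Moving from 54 to 55 per arm changes power by 0.7 to 0.8 percentage points in every comparison.

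**The case against.** The strongest reply is that nothing of substance is lost. The plan attaches 80% power to 45 per group, and 48.6 evaluable per arm exceeds that. If Student's t test is used, which is one of the two tests named for the primary endpoint, and the scale costs no efficiency, power is above 82%. The gap to 110 is two patients, trivial beside the uncertainty in a standard deviation taken from a single evaluation study and in a round 10% dropout guess. The figure of 108 is also not arbitrary: the unrounded base gives 108.18, and 54 per arm agrees with 108 in total.

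Most of this stands, and it limits the point. It does not make the printed equation true, and it does not make the dropout step do its job. Nor can the ordinal allowance simply be counted as spare power, since the plan added it to pay for the ordinal scale and provides for the Mann-Whitney test if normality fails.

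A reader might infer more than the documents support in three ways:

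- *That 108 patients fail to give 80% power, or give a flat 78–79%.* Power falls below 80% only if the entire ordinal allowance is counted as lost efficiency. The article does not say that the loss is that large and gives no efficiency figure for the rank test on this scale. A figure as low as 78.1% appears only if 48.6 is also cut to 48 before dividing by 1.1 and the t distribution is then applied.
- *That the base should be 46 because a t test is planned.* The article prints a normal-approximation formula and evaluates it correctly. Choosing the t-based number is a preference, not a correction.
- *That going to 110 secures 80% on every basis.* With the full ordinal cost it gives 80.3% by the normal approximation but 79.4% by t.

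**Conclusion.** The equation and the dropout step are wrong as written. By the plan's own inputs the randomised total should be 110, against 108 stated, which leaves 48.6 evaluable patients per arm where 49.5 are called for.

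This is a small error in a figure that the trial relies on, not a demonstrated lack of power. With 54 per arm, power is 83.2% (normal) or 82.4% (t) if the ordinal scale costs nothing, and 79.5% or 78.6% if it costs the full 10%.

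These figures assume the plan's difference of 0.32, its standard deviation of 0.54 and exactly 10% dropout in each arm. The 10% efficiency cost is the plan's own allowance, used here as given; the true cost is not in the document. An unconditional 80% does not describe what 54 per arm delivers, and neither does an unconditional 78–79%.

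**What to change.** Correct the calculation so that each step can be followed:

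- 45 per arm from the formula;
- 45 × 1.1 = 49.5 evaluable per arm after the ordinal correction;
- 49.5 / 0.9 = 55 per arm, 110 in total, to retain that number after 10% dropout.

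If 54 per arm is kept, say so. State that 48.6 evaluable patients per arm are expected, and give both conditional power figures: 83.2% (82.4% by t) with no efficiency loss from the ordinal scale, and 79.5% (78.6% by t) if the full allowance is used up. This costs a few lines of text and no patients.

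If the sponsor prefers to meet the 49.5 in full, the target becomes 110. It must then also be changed in the abstract, and the end-of-recruitment and end-of-study statements must be read against it. That is two more patients at a centre that reports about 260 such procedures a year.

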## Discussion

PASSAT is a prospective RCT with a non-randomised side arm which compares the procedure-related patients’ satisfaction with thoracoscopic operations performed in either local anaesthesia, analgosedation and spontaneous breathing (intervention group) or in general anaesthesia with OLV (control group). Despite GA with OLV being the most common anaesthetic technique used in thoracic surgery, the LA and analgosedation technique is a suitable alternative for the surgical management of numerous indications such as pleural diseases and small peripheral resections. However, the awareness of being brought into the operating room, preparation of the surgical field, the surgery itself and of being brought to the postoperative care unit may be a stressor for the patient [41], depending on the staff’s attention toward the patient and her or his stress coping resources.

Furthermore, one has to be aware of intraoperative hypercapnia due to iatrogenic pneumothorax and paradoxical diaphragm movement [16, 19, 42]. To prevent hypercapnia, patients with severely impaired lung function are recommended to be operated on using GA with controlled mechanical ventilation. However, the existing recommendations—which are respected in this study—are based on expert opinions [12, 19]. A single small study evaluated intraoperative carbon dioxide tension during thoracoscopy in LA (*n*=16), but without reporting the patients’ preoperative lung function [43]. To ensure patients’ safety, we will use intraoperative airway capnography in both groups. The data will be continuously recorded and analysed depending on the preoperative pulmonary function.

Since procedures in LA are believed to be cheaper than those in GA but cost estimations from the German health care system are lacking, we will accurately record and compare the costs, including material and personal resources.

Decision making is a process that involves not only medical and economic aspects, but also the patient’s perspective. However, the patient’s perception and procedure-related satisfaction have not yet been properly investigated. Most studies on surgery in LA do not assess patients’ satisfaction at all or do so in an insufficient manner. Satisfaction is influenced by innumerable variables; thus properly designed questionnaires which meet psychometric criteria are required.

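### The primary test is left to a normality check that will almost certainly select Mann-Whitney, which does not address the 0.32-point mean difference the trial is sized on

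*Protocol article*

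**What the plan says.** All of this stands in the Protocol article, Hypothesis and sample size calculation, unless noted.

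- **Endpoint:** the ANP score for satisfaction with anaesthesia. "The score is noted on an ordinal scale from 0 to 3".
- **Hypotheses:** "The null hypothesis is that patients with LA are as satisfied with anaesthesia" on that score as those with GA; "The alternative hypothesis is that satisfaction in both groups is not equal". Neither means nor ranks are named.
- **Sizing:** planning mean 2.58, SD 0.54, relevant difference 0.32 points, "With a significance level of *α*=5*%*, a power of (1−*β*)=80*%* and an allocation rate of 1:1". The formula is the normal one for two means and gives 45 per group. The plan adds 10% because the scale is ordinal and 10% for dropout, and arrives at 108.
- **Primary test:** "After checking for normal distribution, the primary endpoint will be tested with" Student's t or Mann-Whitney U, according to the result. The check, its threshold and the effect measure to be reported are not named.
- **Discussion section:** being aware of the operating room and the surgery "may be a stressor for the patient", depending on staff attention and the patient's coping resources.

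**The concern.** This is a stated rule, not a detail left open for an analysis plan. It lets the trial data decide which of two tests is confirmatory, and the two address different quantities. Student's t compares mean scores. Mann-Whitney compares how often a patient in one arm scores higher than a patient in the other. Clinical relevance and sample size are both expressed as a mean difference of 0.32.

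A score capped close to its planning mean is very unlikely to pass a normality test, so the branch that matches the sizing would probably not be used. The trial would then report a p-value with no estimate to read against 0.32. If LA changes the shape of the score distribution and not only its level, that p-value can point to a difference when mean satisfaction is equal, or miss a mean difference of the size defined as relevant.

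**Working it through.** **1. The plan's own figure.** Inputs from the sample size section: σ = 0.54, ε = 0.32, two-sided α = 5%, power 80%, 1:1.

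n = 2 × (σ × (z₀.₉₇₅ + z₀.₈₀) / ε)² = 2 × (0.54 × (1.960 + 0.842) / 0.32)² = 44.7, so 45 per group. This matches.

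Total: 2 × 45 × 1.1 × 1.1 = 108.9. The plan states 108, i.e. 54 per arm. This matches within rounding. After 10% dropout, 54 × 0.9 = 48.6, so about 48 or 49 per arm are evaluable.

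**2. Which test would the check select?** Headroom to the ceiling: (3 − 2.58) / 0.54 = 0.78 SD. Scores on 0–3 with mean 2.58 and SD 0.54 were simulated at 49 per arm (2,000 runs per setting). The assumed shapes were a discretised beta and a censored normal; the assumed number of score levels was 4, 10, 16 or 31, because the article does not give the item structure. The assumed check was Shapiro-Wilk at 5% in each arm. It rejected normality in 100% of runs in every setting.

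**3. Type I error of the rule as written.** With identical distributions in both arms, check followed by test rejected in 3.4–5.4% of runs, about nominal.

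**4. Power when the spreads are similar.**

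| Means 2.58 vs 2.26 | t | Mann-Whitney |
|---|---|---|
| SD 0.54 in both arms, 49 per arm | 81–83% | 84–96% |
| SD 0.65 in the lower arm, 49 per arm | 74–76% | 71–86% |

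A separate four-level example at 48 per arm gave about 78% for each test.

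**5. Equal means, different shape.** Four levels, 48 per arm. GA shares at 0/1/2/3 are 0/2.5/37/60.5%: mean 0.025 + 0.74 + 1.815 = 2.58, SD 0.54. The LA shares are assumptions:

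- **LA 4/10/10/76%.** Mean 0.10 + 0.20 + 2.28 = 2.58; SD = √(0.10 + 0.40 + 6.84 − 2.58²) = √0.684 = 0.83. Probability that an LA patient scores higher, counting ties as half: (0.76 × 0.395 + 0.10 × 0.025) + ½ × (0.10 × 0.025 + 0.10 × 0.37 + 0.76 × 0.605) = 0.303 + 0.250 = 0.552. Mann-Whitney rejects in about 19% of trials, almost all favouring LA; Welch's t in 5.5%.
- **LA 3/8/17/72%.** Mean 0.08 + 0.34 + 2.16 = 2.58; SD = √(0.08 + 0.68 + 6.48 − 2.58²) = √0.584 = 0.76. The same probability is 0.289 + 0.250 = 0.539. Mann-Whitney rejects in about 13%; Welch's t in 5.4%.

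The mean difference is exactly zero in both cases, while the quantity to which Mann-Whitney responds is not at its null value of 0.5.

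**6. A true 0.32 deficit with wide LA spread.** GA mean 2.58; LA mean 2.26 with assumed SD about 1.0. Mann-Whitney has about 16% power, Welch's t about 46%. Both fall short of 80% because the spread exceeds the planning SD, but Mann-Whitney loses far more.

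**The case against.** **The hypotheses name no means.** The null speaks of equal satisfaction. In the first example of step 5, 76% of LA patients and 60.5% of GA patients reach the top score, and detecting that agrees with the stated alternative. This stands. A reader might call those rejections false positives under the stated null, but the article does not support that. The mismatch is with the quantity used for relevance and sizing.

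**If the check nearly always selects Mann-Whitney, nothing is really chosen from the data.** A reader might infer that the rule inflates the type I error. Step 3 shows that it does not under identical distributions. Nor is the selection certain: the check is unnamed, and a graphical check or a different observed distribution could lead to t.

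**The plan adds 10% for the ordinal scale.** This is an allowance for a rank test. It covers the loss under normality (efficiency 3/π: 45 × π/3 = 47.1, so 48 per group, against 45 × 1.1 = 49.5). It does not cover the theoretical worst case for a location shift (45 / 0.864 = 52.1, so 53). A reader might infer that the trial is too small. Step 4 does not support that: with equal spreads Mann-Whitney has at least the power of t. But a larger sample does not turn a rank test into a test of a mean difference.

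**The polarised LA distributions are assumed.** This stands. The only SD in the article is 0.54. The Discussion's remark on awareness as a possible stressor makes unequal shapes plausible; it does not predict equal means with polarised scores.

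**A rank analysis is defensible for an ordinal score.** It is, provided that the relevant difference is stated on that scale. Here it is stated as a difference in means.

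**Conclusion.** The point holds as a mismatch of target. The article leaves the primary test to a check on the trial data, names no effect measure, and under a formal check would almost certainly end with a test that does not address its own 0.32-point criterion. That near-certainty rests on the planning mean and SD, the 0–3 range, and the assumption of a formal test such as Shapiro-Wilk.

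The cost depends on the shapes of the two distributions. With similar spreads it is small for the p-value, although an estimate on the 0.32 scale would still be missing. With LA SD 0.76–0.83 against 0.54 and equal means, rejection rates are 13–19% against 5–6%. With a true 0.32 deficit and LA SD about 1.0, power is about 16% against 46%. These last figures show what can happen under assumed distributions; they do not forecast this trial.

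The calculations do not show an inflated type I error or a sample size that is too small.

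**What to change.** Before the data are analysed, delete the normality check and fix one primary analysis together with its effect measure. As 0.32 is a mean difference, the consistent choice is the LA-minus-GA difference in mean ANP satisfaction-with-anaesthesia score, tested with Welch's t or a linear model with heteroscedasticity-robust standard errors, and reported with a 95% confidence interval read against 0.32. Name Mann-Whitney as a sensitivity analysis.

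If the investigators prefer a rank-based primary analysis because the score is ordinal, they should name its effect measure (the probability that an LA patient scores higher than a GA patient), restate the relevant difference on that scale, and rest the sample size on it.

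The first option costs one sentence in the protocol or analysis plan and no patients; the 45 per group and 108 in total stand. The second also needs a new justification of the relevant difference and the sample size.
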